Therefore, the present study is designed to show that implant success is not compromised by immediate loading when a single median implant in the edentulous mandible is used to retain a complete mandibular denture. In addition it is the aim of this trial to show that the quality of life and chewing function can be improved earlier by immediate loading with less pain and discomfort for the patient.

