### Outcomes

Implant success according to the modified success criteria of Albrektsson *et al*. [15] has been chosen as the primary outcome of this trial. Secondary outcomes are the earlier improvement in quality of life and chewing function tested using the German version of the oral health impact questionnaire [16] and objective masticatory performance [17].

It is hypothesized that patients with immediate loading will suffer less pain and discomfort during the intervention than patients with second-stage surgery as measured by a questionnaire with a visual analog scale. Prosthetic complications and maintenance interventions, such as adjustment or exchange of retention elements, fracture of the denture base, relining and so on, are recorded and should be comparable in both groups.

Follow-up visits will occur at 1 month and 4, 12 and 24 months after implant loading. In addition, patients in the control group will be examined 1 month after implant placement (Figure 1).

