### Statistical methods

For the primary outcome, the measure for non-inferiority of the success rate of the experimental group compared to the control group will be tested by a one-sided equivalence test for the success parameter of the underlying binomial distributions. The significance level for the one-sided equivalence test is 2.5%. All patients that are randomized and followed up for 24 months as well as all patients with an implant failure will be statistically analyzed. The secondary endpoints (improvement of the chewing efficiency and improvement of the oral health related quality of life after the intervention) will be addressed by non-parametric tests for non-inferiority of the experimental group compared to the control group. Non-inferiority of prosthetic complications will be analyzed by one-sided equivalence tests.

In the case of an implant failure in the experimental group, the patient will be treated according to the protocol of the control group with a new implant. Those patients will be excluded from the trial before retreatment. If more than 20% of the implants fail in any group within the first 3 months after implant placement, the study will be terminated. This criterion will be checked every 6 months after the inclusion of the first patient.

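### Quality of life and chewing function are meant to improve earlier with immediate loading, but the planned non-inferiority tests do not test this directly and no time origin is fixed

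*Protocol article*

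**What the plan says.** All references are to the protocol article.

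- **Background (last paragraph):** "it is the aim of this trial to show that the quality of life and chewing function can be improved earlier by immediate loading".
- **Outcomes:** "Secondary outcomes are the earlier improvement in quality of life and chewing function", measured by an oral-health questionnaire and a masticatory performance test. A separate hypothesis is that "patients with immediate loading will suffer less pain and discomfort during the intervention than patients with second-stage surgery". Prosthetic complications are expected to be similar in the two groups.
- **Outcomes (visits):** follow-up at months 1, 4, 12 and 24 is counted from loading. In addition, "patients in the control group will be examined 1 month after implant placement".
- **Intervention:** the experimental implant is loaded at once, the control implant after 3 months of submerged healing. Randomisation takes place after placement and the stability measurement.
- **Statistical methods:** the secondary endpoints are restated as "improvement of the chewing efficiency and improvement of the oral health related quality of life after the intervention", and these "will be addressed by non-parametric tests for non-inferiority of the experimental group compared to the control group". For complications, "Non-inferiority of prosthetic complications will be analyzed by one-sided equivalence tests". No time point or time origin is given for the comparison of chewing or quality of life, and no test is named for pain.

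**The concern.** The aim and the outcome definition are directional: patients loaded immediately should benefit sooner. The test chosen for these endpoints has a different null hypothesis, namely that the experimental group is worse by at least some margin. Rejecting it supports *not materially worse*, which is a weaker statement than *earlier*.

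The time origin adds to this. The main visits run from loading, and loading differs by 3 months between the groups. An analyst who pairs visits by label would compare the groups at different times since randomisation, and would leave out the interval in which an earlier benefit would appear.

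At stake is a stated secondary aim. The trial could finish with its planned secondary tests all met and still have no direct comparison to cite for the claim that patients benefit sooner.

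**Working it through.** The article gives no effect size, margin or power for these endpoints, so there is no figure of its own to reproduce. The check sets the sections side by side and then works out the visit times.

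**1. Stated direction against named test**

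| Endpoint | Direction (Background, Outcomes) | Test (Statistical methods) | Match |
|---|---|---|---|
| Quality of life, chewing function | earlier improvement | non-parametric non-inferiority of improvement | no |
| Prosthetic complications | similar in both groups | one-sided equivalence (non-inferiority) | yes |
| Pain and discomfort | less | none named in the article | cannot be judged |

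The second row shows that the article fits the test to the aim where similarity is the aim. In the first row it does not. This is a choice of hypothesis made in the article, not a detail left for later.

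**2. Visit times counted from placement**

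Inputs: visits at 1, 4, 12 and 24 months after loading (Outcomes); loading delay 0 months (experimental) and 3 months (control) (Intervention); one extra control visit 1 month after placement (Outcomes).

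Months since placement = loading delay + months since loading.

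| Visit | Experimental | Control |
|---|---|---|
| extra control visit | – | 1 |
| 1 month after loading | 0 + 1 = 1 | 3 + 1 = 4 |
| 4 months after loading | 0 + 4 = 4 | 3 + 4 = 7 |
| 12 months after loading | 0 + 12 = 12 | 3 + 12 = 15 |
| 24 months after loading | 0 + 24 = 24 | 3 + 24 = 27 |

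In every row with the same label the control group is 3 months further from placement. Counted from placement, the experimental group is seen at 1, 4, 12 and 24 months and the control group at 1, 4, 7, 15 and 27. The shared times are months 1 and 4.

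**3. What each pairing measures**

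- Same time since loading: whether function reached after a given loaded period is similar. The 3-month lead does not enter.
- Month 1 after placement: experimental loaded for 1 month, control not yet loaded.
- Month 4 after placement: experimental loaded for 4 months, control for 1 month.

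The last two pairings bear directly on whether improvement comes earlier.

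**4. Illustrative power for a superiority comparison**

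Assumptions: 74 per group, borrowed from Sample size; two-sided 5%; standardised differences *d* assumed; normal approximation.

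Power = Φ(d / √(2/74) − 1.96), with √(2/74) = 0.1644.

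- d = 0.3: Φ(1.82 − 1.96) = 45%
- d = 0.4: Φ(2.43 − 1.96) = 68%
- d = 0.5: Φ(3.04 − 1.96) = 86%
- d = 0.6: Φ(3.65 − 1.96) = 95%

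80% power is reached at d = (1.96 + 0.84) × 0.1644 ≈ 0.46. For a rank test with efficiency 0.955 under normality this is 0.46 / √0.955 ≈ 0.47.

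**The case against.** The strongest reply is that non-inferiority can be a sensible route to the aim. If the experimental group 1 month after loading is not materially worse than controls 1 month after loading, it has reached a similar level about 3 months sooner, because the delay is fixed by design. A non-inferiority confidence interval can also be read for superiority if that is prespecified. Both points stand. A reader might therefore infer from the mismatch that earlier improvement can never be shown, or has no support whatever the effect size, but the document does not bear that out. Loading-based non-inferiority gives indirect support, and the schedule contains shared times since placement. What remains is that the support is indirect: it combines a result within a margin with a design fact and leaves the difference during the first months unestimated. The article also does not prespecify reading the interval for superiority.

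A second reply is that Statistical methods nowhere says that visits with the same label will be compared, and that the time origin may be in an analysis plan not shown here. This is fair, and the loss of the head start is accordingly stated only as a condition. The mismatch between aim and test does not depend on it.

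A third reply is that the power figures rest on assumed effects, a normal formula and the number planned for the 24-month endpoint. That is also right. They show only that a superiority comparison would be worthwhile for moderate effects; they are not evidence of a defect.

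**Conclusion.** The point holds as a mismatch between stated aim and stated test, confined to oral-health quality of life and chewing function. Background and Outcomes call for evidence of earlier improvement. Statistical methods provides only for non-inferiority of improvement and fixes no time origin. If the comparison is made by time since loading, the 3-month lead is not measured. This should be corrected, but it concerns secondary endpoints and leaves the primary analysis untouched.

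Two stronger readings are not supported:

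- *Pain is tested only for non-inferiority.* Statistical methods names no test for pain, and an analysis plan may supply one. The hypothesis of less pain in Outcomes is not contradicted.
- *The trial cannot show the benefits that justify the 7-point margin.* Sample size bases the margin on avoiding a second procedure, a stable denture straight after surgery, and probably less pain. The first follows from the design and the second is what immediate loading is meant to provide. Quality-of-life scores and chewing tests are not named there.

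The conclusion assumes that time since placement is effectively time since randomisation, as Intervention implies, and that visits occur close to schedule.

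**What to change.** For oral-health quality of life and chewing function, prespecify non-parametric superiority comparisons by time since implant placement (randomisation), in this order:

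1. **Month 1:** the experimental 1-month visit against the control group's extra visit 1 month after placement.
2. **Month 4:** the experimental 4-month visit against the control visit 1 month after loading.

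Keep the non-inferiority tests for the later visits and state that those are timed from loading. Reword the endpoint in Statistical methods so that it agrees with Outcomes.

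**Cost:** mainly wording, since all these visits are already scheduled. The one practical condition is that the questionnaire and the chewing test are both used at the control group's 1-month-after-placement visit, which the article does not confirm. If they are not, they have to be added to that visit. Recruitment was already under way (Trial status), so for controls who passed that visit without these measures the data cannot be recovered, and only the month-4 comparison is available for them.

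### Experimental patients leave the trial at implant failure and no rule is stated for control failures, so secondary comparisons after a failure can be biased towards the experimental group

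*Protocol article*

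**What the plan says.** All the relevant rules are under Statistical methods in the protocol article.

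- **Failure rule.** "In the case of an implant failure in the experimental group, the patient will be treated according to the protocol of the control group". This includes placing another implant. The next sentence reads: "Those patients will be excluded from the trial before retreatment". The rule names the experimental group only. Nothing is said there about control failures, and the removal list under Stopping criteria does not name implant failure for either group.
- **Analysis set.** "All patients that are randomized and followed up for 24 months as well as all patients with an implant failure will be statistically analyzed".
- **Secondary tests.** Two endpoints are named: "improvement of the chewing efficiency and improvement of the oral health related quality of life after the intervention". On the method, the article says that these "will be addressed by non-parametric tests for non-inferiority of the experimental group compared to the control group". For complications: "Non-inferiority of prosthetic complications will be analyzed by one-sided equivalence tests". No value or rank is given for a patient whose implant has failed.
- **Visits** (Outcomes section). "Follow-up visits will occur at 1 month and 4, 12 and 24 months after implant loading".

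**The concern.** Exclusion ends trial follow-up. An experimental patient whose implant fails has no trial chewing or quality-of-life score at any later visit, and complications stop being counted. For the binary primary endpoint this does no harm, because the failure is itself the outcome. For the secondary endpoints, the experimental patients seen after a failure has occurred are those whose implant still stands. Implant survival is decided after randomisation, and it is the very outcome on which the trial compares the two loading protocols.

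Two features make this matter. First, the secondary tests are non-inferiority tests, so losing the worst-off experimental patients pushes towards the favourable conclusion. Second, the Sample size section defends the 7-point margin by the benefits to patients of immediate loading. If immediate loading costs some additional implants, the secondary outcomes should show whether the benefit survives that cost. Under the rule, the patients who bear the cost are absent from the later comparisons.

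The Sample size section also assumes that the reasons for loss are unrelated to the assigned group. An exclusion triggered by failure and written for one group does not fit that assumption.

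**Working it through.** The plan gives no figure on this point to reproduce, so the check is an illustration from its own inputs.

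**Inputs**
- 90 patients randomised per group (Sample size).
- Control failure fC = 0.03, from the assumed 97% success (Sample size).
- Experimental failure fE in four cases: 0.03 (planned); 0.10 (97% less the 7-point margin, so 90% success); 0.176 (immediate-loading study cited in Background, at 12 months); 0.20 (termination limit in Statistical methods, which applies to the first 3 months).
- Assumptions: survivors have the same score distribution in both groups, and each rate is the share failed by the visit analysed. The cited rates refer to different times, so the cases are scenarios and not forecasts.

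**Experimental patients affected, 90 × fE:** 2.7, 9.0, 15.8 and 18.0.

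**Probability that an experimental patient does better than a control patient (ties count one half)**

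Survivors only: 0.50 in every case. This follows from the assumption of identical survivors.

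Failures in both groups ranked worst:

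P = 0.5(1 − fE)(1 − fC) + (1 − fE)fC + 0.5 fE fC, which simplifies to 0.5 − 0.5(fE − fC).

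| fE | fC | Calculation | P |
|---|---|---|---|
| 0.03 | 0.03 | 0.47045 + 0.0291 + 0.00045 | 0.500 |
| 0.10 | 0.03 | 0.4365 + 0.0270 + 0.0015 | 0.465 |
| 0.176 | 0.03 | 0.39964 + 0.02472 + 0.00264 | 0.427 |
| 0.20 | 0.03 | 0.3880 + 0.0240 + 0.0030 | 0.415 |

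**Unequal handling.** If experimental failures leave but control failures stay with the worst rank:

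P = 0.5(1 − fC) + fC = 0.485 + 0.03 = 0.515, whatever fE is. This holds even with 3% failure in both groups, where the even-handed value is 0.500.

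**On the scale of mean improvement.** If a failure counts as zero improvement, a survivor-only difference of 0 becomes (1 − fE) − (1 − fC) = fC − fE once failures are counted. That is 0, −0.07, −0.146 and −0.17 of the survivors' improvement in the four cases.

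No such figure can be worked out for prosthetic complications, because the article gives no expected complication rate.

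**The case against.** **A reader might infer that the secondary endpoints are analysed in survivors only throughout.** The article does not say so. Its analysis-set sentence keeps every patient with a failure and is not limited to the primary endpoint. Scores and complications from before a failure also exist, and the stated secondary aim is earlier improvement, which does not rest on the last visit alone. This stands: the selection concerns visits after a failure. But keeping a patient in the analysis set supplies no score where none was collected, and no rank is fixed in its place.

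**A reader might infer that the rule favours the experimental group in any event.** It does not. At the planned 3% in both groups with equal handling the shift is zero. At an assumed 5% against 3%, P is 0.5 − 0.5 × 0.02 = 0.490, a shift of only 0.01. Silence about control failures in a condensed article is also not a rule that they stay in.

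**The larger shifts belong to scenarios in which the primary test should fail.** 10% against 3% lies on the non-inferiority boundary, and at 17.6% a positive primary result is very unlikely. The 17.6% comes from a small study, for which the Discussion mentions 17 implants. This stands too. No secondary margin is given either, so it cannot be shown that a particular conclusion would reverse.

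**The scoring may be settled in the analysis plan or the full protocol, which are not shown.** That is fair for the scoring, and its absence from the article is not the criticism. The exclusion, however, is a stated rule. A later plan can assign a rank, but it cannot recover scores that were never collected.

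**Follow-up after retreatment is not a clean remedy.** These patients are then treated under the control protocol, so their later scores could pull the groups together, which is also anti-conservative for non-inferiority. This stands and narrows the fix.

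**Conclusion.** The point holds in a conditional form and for secondary outcomes only. The stated rule ends secondary data collection at failure in the experimental group, with no counterpart for controls. Comparisons at later visits can therefore be biased towards that group. The bias needs either more experimental failures (0.50 among survivors against 0.465 at 10% and 0.427 at 17.6%, with 3% in controls) or control failures that stay in with poor scores (0.515 at equal 3% failure). These figures assume identical survivors and failures ranked below every survivor. With equal rates and equal handling the shift is zero.

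It would be wrong to conclude that the trial conceals its failures. They count in the primary endpoint, which this rule leaves untouched.

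**What to change.** Leave clinical management as it is and change the analysis rules:

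1. State one rule for implant failures that applies to both groups.
2. Keep every randomised patient with a failure in the chewing and quality-of-life analyses, in the assigned group, with the worst rank at visits after the failure. The planned tests are already non-parametric, and the failure status is recorded for the primary endpoint.
3. Report the survivor-only comparison as supportive.
4. For prosthetic complications, where worst-rank scoring does not fit, count events up to failure and report the failures alongside them in both groups.
5. Where feasible, go on collecting the scheduled scores after failure for a supportive as-randomised analysis, and note that they partly reflect retreatment.

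The cost is slightly more analysis work and, for item 5, possibly a few extra scheduled visits. Worst rank is also a choice of what to estimate: it places a failure below any score a survivor can have, and the plan should say so. The secondary result will look less favourable if experimental failures are more frequent.

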### Recruitment

Recruitment of patients will be performed in two steps. Edentulous patients who have signed the informed consent will be screened according to the inclusion and exclusion criteria applying standardized examination forms and questionnaires including the SCL-90-index. Patients who otherwise meet the inclusion criteria but whose complete dentures are judged not to be technically acceptable will be referred for denture revision or new dentures. They will be offered the opportunity to be examined again after these improvements to the denture for possible inclusion in the trial if the dentures can be worn for at least 3 months before the recruitment period ends.

Patients meeting the inclusion criteria regarding denture status, denture satisfaction and SCL-90-index will undergo a radiographic examination (panoramic x-ray with reference marker) to determine whether the residual bone height of the mandible meets the inclusion criteria. To achieve consistent evaluation of the x-rays, the trial coordinator will assess all x-rays from each patient and perform the required measurements. For quality assurance, each patient’s documents will be sent pseudonymized to the treatment coordinator, who will make the final decision on inclusion in the study. If all inclusion criteria are met, patients will be included in the study.

## Discussion

This randomized clinical trial is designed to show the suitability of immediate loading of single median implants in an edentulous mandible. It is hypothesized that there will be non-inferiority of implant success for the experimental group compared to the control group.

Present clinical trials investigating a single midline implant in an edentulous mandible are mostly designed with a small number of patients [6,19,20]. Due to the sample size required for our clinical trial, a multi-center design is necessary. Taking into account a loss to follow-up rate of approximately 20%, a total of 180 patients (90 per group) was considered necessary. The loss to follow-up rate of 20% appears rather conservative but this rate also takes into account the exclusion of patients due to stopping criteria, e.g. compromised implant stability. In one study on immediate loading of a single mandibular implant, only 1 out of 17 implants (5.9%) did not achieve a minimum insertion torque of 30 Ncm [6]. In another study of immediate loading, only 2 out of 27 implants (7.4%) with oxidized surfaces did not achieve an insertion torque of 45 Ncm; however, the insertion torque actually obtained for these two implants was not reported [20]. From these studies, it is assumed that in our trial the number of patients excluded due to compromised implant stability and loss to follow-up will be less than 20%.

In a pilot study conducted at the University of Kiel, 11 patients were treated with one median implant in the mandible [21,22]. During this pilot trial, six implants followed a non-submerged healing protocol and were provided with a healing abutment and thus loaded moderately. No implant failed. The initial idea for the present clinical trial was to design a third treatment group as another experimental group with implants healing unsubmerged and moderately loaded over the healing abutment. However, for this three-arm study design, 354 patients would need to be allocated to the trial, as 282 patients would be needed for analysis. This number of patients would not have been feasible, especially in terms of finance. The idea of the present clinical trial is to compare two different healing protocols and not two different treatment options. The non-inferiority of one versus two implants in an edentulous mandible was shown by Walton *et al*. in 2009 [11]. A third treatment group with two implants in the interforaminal area was thus not considered necessary.

The defined inclusion criteria seem to be rather conservative, especially in terms of the residual bone height. We decided to include patients measured as McGarry Class II and III only. Patients with a residual bone height of 10 mm or less as the lowest vertical height of the mandible (Class IV) are excluded due to the risk of a rotational axis in the implant area and insufficient bone support of the mandibular overdenture in the posterior region. Patients with a residual bone height of 21 mm or greater as the lowest vertical height of the mandible (Class I) are excluded as well. It was expected that those patients’ quality of life related to oral health and prosthodontic satisfaction would already be at a rather high level and would not be significantly improved with an implant therapy requiring surgical intervention. It was estimated that 230 people assessed for eligibility would result in 180 people being allocated to the trial (an exclusion rate of 21.7%). So far, 19.1% of patients who have undergone screening have had to be excluded due to insufficient bone according to McGarry [14]. The residual bone height seems to be a major factor when considering edentulous patients for implant therapy. Psychological factors were of minor importance. Due to the high exclusion rate after screening during the first 8 months of recruitment, the recruitment period was extended until March 2014.

